### Secondary outcomes

Cost-effectiveness will be assessed based on health-related quality-of-life (HRQoL) and cost estimates. HRQoL (self-report and proxy-report) is measured using the EQ-5D-3L and ReQoL-UI, the latter derived from the ReQoL-10, recorded at baseline, 19 and 38 weeks post-randomisation. Costs are based on unit costs applied to an assessment of intervention and healthcare use recorded at 19 and 38 weeks post-randomisation.

#### EQ-5D-3L

The EQ-5D-3L has a self-report version that has been adapted to ease the burden on participants with mild to moderate intellectual/learning difficulties/disabilities (adapted EQ-5D-3L; see Appendix B). The adapted EQ-5D-3L questionnaire is completed by the participant and the EQ-5D-3L Proxy Version-1 by ward staff at baseline, 19 weeks and 38 weeks post-randomisation. The questionnaire is completed by a member of staff who is familiar with the participant’s general health; however, it may not always be completed by the same person, so we are recording who has conducted each assessment.

The questionnaire consists of two sections: the descriptive system and the visual analogue scale (VAS). The descriptive system in the adapted questionnaire comprises the following five categories aligned with the traditionally used EQ-5D-5L, each describing a different aspect of health: mobility (i.e. ‘walking about’), self-care (e.g. ‘looking after myself’), usual activities (e.g. ‘doing things I want to do’), pain/discomfort, and anxiety/depression (e.g. ‘feeling worried, sad, or unhappy’). Each category has 3 response options: no problems, some problems, extreme problems (labelled 1–3). There should be only one response for each dimension. Missing values are coded as ‘−9’. Ambiguous values (e.g. two boxes are ticked for a single dimension) are treated as missing values. This part of the questionnaire provides a descriptive profile that can be used to generate a 5-digit health state profile that represents the level of reported problems on each of the five dimensions. For example, ‘11,223’ indicates no problems with mobility and self-care, some problems with usual activities and pain/discomfort, and extreme problems with anxiety/depression. While state ‘11,111’ indicates no problems on any of the five dimensions. A utility-based (aka, preference-based) value set can be applied to the health state profile score, facilitating the calculation of quality-adjusted life years (QALYs). In this trial, we are using the EQ-5D-3L value set derived for the UK using a standardised valuation exercise, in which a representative sample of the general population is asked to place a value on EQ-5D-3L health states using the time trade-off valuation technique [18]. UK value set scores range from − 0.594 (where 0 is a health state equivalent to dead; negative values are states suggested to be worse than dead) to 1 (perfect health) [18].

The second part of the questionnaire consists of a horizontal VAS on which the nurse rates the participant’s perceived health from 0 (worst imaginable health) to 100 (best imaginable health). The participant will complete an amended horizontal VAS, rating their health from 0 to 10 [19].

#### ReQoL-10 and ReQoL-UI

The ReQoL-10 questionnaire is completed by the participant and ward staff (as a proxy) at baseline, 19 and 38 weeks post-randomisation. For the proxy-report, we have specified that at each time point both the EQ-5D-3L and ReQoL-10 should be completed by the same proxy (i.e. same member of ward staff) and where possible it should be the same proxy across time points, but we recognise that might not always be possible. We are recording who has completed each assessment.

ReQoL-10 consists of 10 mental health questions and one physical health question. Although physical health is important to the quality of life of mental health service users, it is not included in the ReQoL-10 summary score because it is distinct from mental health. Each question is scored from ‘None of the time’ to ‘Most of the time’. There are 6 positively worded questions (Q2, 4, 5, 7, 8, and 10), scored from 0 to 4 and 4 negatively worded questions (Q1, 3, 6, and 9), scored from 4 to 0. An overall summary score is calculated by summing the scores of the 10 questions. The ReQoL-10 score can range from 0 (indicating the poorest quality of life) to 40 (indicating the highest quality of life). If a single question is unanswered, the ReQoL-10 developers suggest the mean value of the other responses can be used. If more than one question is unanswered, the overall summary score cannot be calculated. If respondents give two answers to a single question, we will record the response which represents the poorer state [20].

The ReQoL-UI classification system, developed by Keetharuth et al. [21], is based on 7 ReQoL-10 items: 3 positively (ReQoL-10 items: 5, 7, 10) and 3 negatively (ReQoL-10 items: 3, 6, 9) worded mental health items, and its one physical health item. These 7 items cover 7 themes of self-reported recovery-focused quality of life: autonomy, wellbeing, hope, activity, belonging and relationships, self-perception, and physical health. The ReQoL-UI is described as having 2 overall dimensions: a mental health (6 items) and a physical health (1 item) dimension. ReQoL-UI score ranges from − 0.195 to 1, which can be used to estimate QALYs.

#### Healthcare resource use and costs

Adults within secure care, such as the SCHEMA trial participants, have limited access to external health and social care services. As such, resource use for the trial analyses is limited to those healthcare resources that are recorded on the secure care electronic care systems for the trial participants. For example, this includes attendance at a special hospital, specialist assessment, and acute psychiatric ward admission, alongside specific staff contacts and medications. This healthcare data is collected by a combination of research staff and ward staff at 19 weeks and 38 weeks post-baseline. The resource use data is recorded within a proforma resource use measure (RUM) as part of the eCRF for the previous 19-week period since baseline or last RUM data collection time-point, i.e. each RUM is focused on the previous 19 weeks since the current point of data collection. The process involves research staff checking the patient notes for what resources the patient has used based on a proforma, which they then confirm with ward staff. As such, the healthcare data represents routinely recorded data for the trial participants, rather than self-reported, which avoids certain issues with self-reported data (e.g. recall measurement error or bias) [22]. The proforma RUM is presented within Appendix C. Through discussions with the SCHEMA TMG, RUM data is not collected at baseline to limit the data collection burden at baseline. Also, through TMG discussion, baseline resource use (i.e. resource-use consumption 19 to 38 weeks pre-baseline) was perceived not to be prognostic of resource use consumption (or other trial outcomes) over the proceeding 38 weeks post-baseline, limiting the use of baseline RUM data.

Unit costs are assigned to the resource-use information collected within the RUM to calculate total costs for each type of resource use and per trial participant [23]. Unit costs are sourced from data sources relevant to the NHS within England; this includes the National Schedule of NHS costs (e.g. for secondary care costs), Personal Social Services Research Unit (PSSRU) costs of health and social care (e.g. for staff costs), and British National Formulary (BNF; e.g. for medications) [24–26].

Unit costs will be sourced for the more recent year available at the time of attaching unit costs to the resource use data (e.g. 2024/2025) with costs prior to this year inflated using an appropriate inflation index (e.g. NHS Cost Inflation Index) [25].

The costing perspective will be that of the NHS, given the limited range of external services available or required to those within secure care. A societal perspective is not considered a relevant secondary analysis for these trial participants. The frequency/severity of aggressive incidents as measured by the MOAS (as described above) at week 38 post-randomisation.2.Longitudinal changes in aggressive behaviour are assessed weekly between 19 and 38 weeks post-randomisation using the MOAS score (as described above).3.Patient distress attributed to psychiatric symptoms is assessed at baseline, 19 and 38 weeks post-randomisation using the Brief Symptom Inventory (BSI) Positive Symptom Distress Index (PSDI).

The Brief Symptom Inventory (BSI) is a 53-item self-report instrument designed to assess psychological symptoms over the past week. The BSI is composed of nine primary symptom dimensions (somatization, obsessive–compulsive, interpersonal sensitivity, depression, anxiety, hostility, phobic anxiety, paranoid ideation, and psychoticism). Participants rate the extent to which a specific problem has distressed them in the past 7 days, using a 5-point scale (0 = not at all to 4 = extremely). Scores are determined by summing values for each symptom dimension and then dividing by the number of items in the respective dimension. The Positive Symptom Total (PST) is the number of items with a positive (nonzero) response and the Positive Symptom Distress Index (PSDI) is the sum of the values with positive responses divided by the PST. Raw scores can be converted to standardised *T* scores, generating a profile that graphically illustrates a respondent’s current psychological symptom presentation [17]. The BSI PSDI is recorded at baseline, 19 and 38 weeks to assess changes in patient distress attributed to psychiatric symptoms.

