### Timing of outcome assessments

Outcome assessments (Table 2) are conducted at baseline (prior to randomisation), 19 and 38 weeks post-randomisation with a ± 2 weeks window.

**Table 2 Tab2:** Schedule of enrolment, interventions, and assessments

Procedures	Screening	Baseline	Randomisation	Treatment phase	19 weeks	Weekly	38 weeks	Ad hoc
Informed consent	X							
Eligibility assessment	X							
LDSQ	X							
Treatment allocation			X					
Demographics		X						
Medical history		X						
Q1 HONOS (WAA or LD)	X							
Randomisation		X						
Delivery of intervention				X				
Compliance				X				
MOAS		X			X	X	X	
EQ-5D-3L self-reported LD adapted version*		X			X		X	
EQ-5D-3L Proxy Version 1		X			X		X	
Resource use					X		X	
ReQoL-10 Self Report version		X			X		X	
ReQoL-10 Proxy reported**		X			X		X	
BSI		X			X		X	
Adverse event assessments								X
Physician’s withdrawal checklist								X

*LDSQ* Learning Disability Screening Questionnaire, *Q1 HONOS (WAA or LD)* Item 1 of the Health of the Nation Outcome Scale (Working Age Adults or Learning Disabilities), *MOAS* Modified Overt Aggression Scale, *BSI* Brief Symptom Inventory

*EQ-5D-3L self-reported using LD (learning disabilities) adapted version

**ReQoL-10 Self-Report version completed by a proxy

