## Economic evaluation

Cost-effectiveness analysis via cost per quality-adjusted life year (QALY) is recommended internationally, including by the National Institute for Health and Care Excellence (NICE) for England and Wales [42]. Therefore, in adults within secure care who have borderline to mild/moderate ID, we will calculate the mean incremental cost per QALY of interpersonal art psychotherapy compared to usual care over 38 weeks, from a healthcare perspective.

Cost-effectiveness will be inferred when comparing our incremental cost-effectiveness results to a relevant cost-effectiveness threshold, such as thresholds from £0 (whereby cost savings are preferred to QALY gains) up to £50,000 per QALY, with specific attention to £20,000 to £30,000 per QALY thresholds as suggested by NICE [42].

The primary QALY-based analyses will use the self-reported, adapted EQ-5D-3L, albeit its use has implications/complications (see the ‘Discussion’ section). To calculate QALYs, the area-under-the-curve (AUC) will be calculated using the data collected for the EQ-5D-5L and ReQoL-UI at baseline, 19 weeks, and 38 weeks [50].

The economic evaluation will be conducted on an ITT basis, based on guidance by Hunter et al. [50] and Franklin et al. [23]. To calculate mean incremental costs and QALYs, both observed and (regression) adjusted mean values will be estimated and compared [44]. Choice of regression model for the adjusted analyses will follow the choices also made for the statistical analyses of the primary outcome (e.g. generalised linear-mixed models) as will the choice of other covariates, while also considering the relevant prognostic nature of the covariate to the economic evaluation outcomes of interest (e.g. baseline utility for QALYs) [50].

Incremental cost-effectiveness ratios (ICERs) will be calculated based on incremental costs over incremental QALYs as the estimated mean difference between the two trial arms. The ICER represents the cost per QALY of the intervention-arm compared to control-arm which will be compared to a relevant cost-effectiveness threshold to infer ‘cost-effectiveness’ or not.

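### The resource-use form has two look-back rules that part company whenever a visit moves within its ±2-week window, and the plan does not say which one governs

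*Protocol article*

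**What the plan says.** All references are to the protocol article.

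- **Healthcare resource use and costs, first rule.** The RUM is completed "for the previous 19-week period since baseline or last RUM data collection time-point". The period starts at an event: baseline for the first form, the previous form for the second.
- **Same sentence, second rule.** After an explanatory i.e., "each RUM is focused on the previous 19 weeks since the current point of data collection". The period now has a fixed length, counted back from the day of collection.
- **Timing of outcome assessments.** Visits are at "19 and 38 weeks post-randomisation with a ± 2 weeks window", and Table 2 places resource use at both of them.
- **Economic evaluation.** The target is the "mean incremental cost per QALY of interpersonal art psychotherapy compared to usual care over 38 weeks".
- **Anchor.** The resource-use section has the data "collected by a combination of research staff and ward staff at 19 weeks and 38 weeks post-baseline", whereas Secondary outcomes has "intervention and healthcare use recorded at 19 and 38 weeks post-randomisation". Baseline assessment precedes randomisation.
- **No baseline form.** "RUM data is not collected at baseline to limit the data collection burden at baseline".

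**The concern.** The two rules describe the same period only when both visits are exactly on schedule. When a visit is early or late, staff following the second rule and staff following the first would extract different weeks from the same notes. The text shown has no rule for an off-schedule visit.

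At stake is the match between the costs and the horizon for which the incremental cost, the ICER and the acceptability curves are reported. Under the fixed look-back, some post-randomisation weeks can drop out and others can count twice. Weeks before randomisation, which cannot carry a treatment effect, can also enter the total. Because two 19-week windows always add up to 38 weeks, a check on total length would not reveal any of this.

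The mixed baseline and randomisation wording adds a smaller doubt about where the first period begins.

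**Working it through.** **Inputs.** Week 0 is randomisation. The first visit is at t1, between 17 and 21, and the second at t2, between 36 and 40 (Timing of outcome assessments). The look-back is 19 weeks (Healthcare resource use and costs). The target period is weeks 0 to 38 (Economic evaluation). Write d1 = t1 − 19 and d2 = t2 − 38; each lies between −2 and +2.

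**Plan's own figure.** With t1 = 19 and t2 = 38, both rules give 0–19 and 19–38: 38 weeks, with no gap or overlap.

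**Fixed 19-week rule.** The windows are [t1 − 19, t1] and [t2 − 19, t2], so:

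- weeks missed = max(d1, 0) + max(−d2, 0) + max(d2 − d1, 0)
- weeks counted twice = max(d1 − d2, 0)
- weeks before randomisation = max(−d1, 0)
- weeks after week 38 = max(d2, 0)

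| t1, t2 | Windows | Missed | Twice | Before 0 | After 38 |
|---|---|---|---|---|---|
| 19, 38 | 0–19, 19–38 | 0 | 0 | 0 | 0 |
| 17, 40 | −2–17, 21–40 | 4 | 0 | 2 | 2 |
| 21, 36 | 2–21, 17–36 | 4 | 4 | 0 | 0 |
| 21, 38 | 2–21, 19–38 | 2 | 2 | 0 | 0 |
| 19, 36 | 0–19, 17–36 | 2 | 2 | 0 | 0 |
| 17, 38 | −2–17, 19–38 | 2 | 0 | 2 | 0 |
| 19, 40 | 0–19, 21–40 | 2 | 0 | 0 | 2 |
| 17, 36 | −2–17, 17–36 | 2 | 0 | 2 | 0 |
| 21, 40 | 2–21, 21–40 | 2 | 0 | 0 | 2 |

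The worst case is 4/38 = 10.5% of the weeks; one visit off by 2 weeks gives 2/38 = 5.3%. In every row the weeks missed equal the sum of the other three columns, because the total is always 19 + 19 = 38.

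**A typical size, by assumption.** The article gives no distribution of visit dates. If d1 and d2 were independent and uniform on (−2, 2), the mean of max(d1, 0) and of max(−d2, 0) would be 0.5 each. The mean of max(d2 − d1, 0) would be half of 4/3, or 0.67. The average missed would then be about 0.5 + 0.5 + 0.67 = 1.7 weeks, with 0.7 counted twice and 0.5 before randomisation. A simulation of 3,000 pairs of dates gave 1.67, 0.67 and 0.50. Visits clustered near the nominal date would give less.

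**Event-anchored rule.** The windows are [0, t1] and [t1, t2]. They adjoin for every permitted pair of dates: no gap between forms, nothing counted twice, nothing before week 0. The total length is t2, so 36 to 40 weeks (2/38 = 5.3% either way). At most 2 weeks are missed at the end, or 2 added beyond week 38.

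**Anchor.** If the first form starts at baseline instead of randomisation, even this rule includes the interval between the two. Its length is not given. The Randomisation section has allocation generated once baseline data are entered, which suggests that it may be short.

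**The case against.** The strongest reply is that the sentence already contains a sound rule. It names baseline or the last form as the start, and the second clause may be no more than shorthand for the nominal 19-week spacing. On that reading nothing is missed between forms, counted twice or taken from before baseline, and what remains is ordinary visit-window variation of at most 2 weeks. Appendix C, which holds the form, is not shown and may carry date fields that settle the matter. This stands in part: the fixed look-back cannot be treated as the rule actually applied. But the clause is written as the meaning of the one before it, the two disagree off schedule, and the main text does not choose between them.

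Three stronger inferences are tempting, and the documents do not support them:

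- **That 10.5% is an error in cost.** It is a share of weeks. Each missed week is matched by a week counted elsewhere, so cost changes only as far as use differs between those weeks. The article gives no figures on that.
- **That incremental cost is biased between arms.** This would need, for example, visit timing that differs by arm. Both arms have the same schedule and window, and nothing says that visits in one arm are delayed.
- **That costs drift while QALYs stay fixed at 0–38 weeks.** Utilities are collected at the same movable visits, so under the event-anchored rule costs and utilities share their dates.

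A further fair point concerns the remedy. Cutting every participant's costs at fixed calendar days would require a return to the notes after an early second visit, and could put costs out of step with utility dates.

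**Conclusion.** The point holds as an internal contradiction with a limited effect. The two look-back rules agree only for visits at exactly 19 and 38 weeks.

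If the fixed rule is followed, up to 4 of 38 weeks are missed, up to 4 are counted twice, and up to 2 pre-randomisation weeks are charged. The 4-week figures need the two visits to move by the full 2 weeks in opposite directions. If the event-anchored rule is followed, those errors vanish and the costed time is 36 to 40 weeks.

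These figures rest on the stated window and look-back and on taking week 0 as randomisation. Which rule the sites used, the effect on mean cost and any difference between arms cannot be determined from the article. The primary outcome is untouched. The correction is minor, but worth making before costs are analysed, so that the choice of rule is not made with the data in view.

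**What to change.** 1. Delete the clause that counts 19 weeks back from the day of collection.
2. State that the first RUM runs from the date of randomisation to the first RUM date, and the second from that date to the second RUM date. Use randomisation as the only anchor, in place of the mixed wording.
3. Record the start and end date of each form.
4. Put costs and QALYs on the same 38-week horizon using the actual dates, by truncation or by scaling. Scaling would multiply by 38/36 = 1.056 for a second visit at week 36 and by 38/40 = 0.95 at week 40. Intervention cost, which follows from sessions delivered, should be kept out of the scaling.

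The cost is a few lines in the plan. The real burden is in forms already completed: the plan was approved on 04/02/25 with the last follow-up expected on 12/04/2025, so many probably exist, across 8 Trusts. Some will need their dates checked or their periods re-queried. The source is the patient notes on the secure care electronic systems, so this should be feasible, but the article does not say that the form itself captures dated entries. Where it does not, scaling by the form dates is the lighter option for forms known to have run end to end.

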## Statistical analyses

The summary of the analysis plan is shown in Table 3.

**Table 3 Tab3:** Summary of the analysis plan

Variable	Intention-to-treat cohort
Baseline characteristics	Descriptive statistics by the trial arms
Primary outcome	• Histograms and other graphical presentation • Linear mixed-effect regression model • Homoscedastic and heteroscedastic regression models
Secondary outcomes	• Histograms and other graphical presentation • Repeated measures ANCOVA model • Linear mixed-effect models
Safety outcomes	Chi-square test
Subgroup analyses	Linear mixed-effect regression model with an interaction term
Sensitivity analyses	Multiple imputation

### Descriptive statistics: baseline and other time-points

Baseline characteristics will be summarised by trial arm using appropriate descriptive statistics.

Categorical data will be summarised by numbers and percentages. Continuous data will be summarised by means (SD) if data are normally distributed and medians (IQR) if data are skewed. Minimum and maximum values will also be presented for continuous data. Summary statistics will be visualised using appropriate graphical plots, including bar graphs, histograms, and boxplots. Baseline and outcome measures will be summarised overall and by trial arm. Tests of statistical significance will not be undertaken for baseline characteristics; rather, the clinical importance of any imbalance will be noted in the trial report. Baseline data will also be summarised for those who completed follow-up compared to those lost to follow-up (i.e. no data at weeks 19 and 38) to assess possible dropout bias.

For the economic analyses, descriptive statistics will focus on the EQ-5D-3L and ReQoL-10 item scores and utility scores, QALYs, resource-use and costs across all resource-use items. Intervention resource-use and costs will also be presented separately to the downstream resource-use and cost descriptive statistics, i.e. the resource-use and cost associated with interpersonal art psychotherapy. All descriptive statistics will be provided as stratified by trial-arm, at/up to each data collection time-point (i.e. at baseline, at/up to 19 weeks and 38 weeks), and across all time-points (i.e. over 38 weeks) as appropriate.

